### Statistical methods

The null hypothesis, according to which the within-subject change of the outcome between T0 and T1 will be the same for the intervention and the control group against a two-sided alternative (immediate effect), will be tested using a linear mixed-effects model with two nested random effects, where the paired families will be first level no. 1 and the family the second level no. 1. The model will be adjusted for factors which are likely to affect the outcome. In the same manner, we will assess the null hypothesis about the within-subject change of the outcome between T0 and T2 (medium term effect) and between T0 and T3 (long term effect). *P*-values will be adjusted for multiple comparisons using the Holm’s method. Analyses will be performed using the R Statistical Software.

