### Eligibility criteria

Families will be eligible for inclusion according to the following criteria: at least one parent is treated for a mental disorder (according to DSM-5 or ICD-10 diagnostic criteria) and at least one child in the family is aged 6–18.

Exclusion criteria for families: parental substance or alcohol dependence that is currently untreated; an acute mental disorder with significant and distressing symptoms including suicidal tendencies that requires an immediate treatment for both children and parents; parental inability to provide consent due to intellectual disability; language barrier.

Eligibility criteria for therapists implementing the ChildTalks+ intervention: professional competence to work with families; ability to adapt the content and language of sessions to the type of parent’s disorder and the age group of the child (ren) involved; completion of training in the ChildTalks+ intervention; motivation to actively participate in the project.

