### Procedure

Therapists will be recruited by a therapist coordinator in collaboration with the project coordinator. Once trained, ChildTalks+ therapists will begin working with families. They will first give the potential candidates information about the ChildTalks+ intervention and about participation in the study. This research study is an essential part of project Implementation and Evaluation of ChildTalks+ in the Czech Republic. If potential candidates express interest, they will be asked if they agree that their other family members be contacted, because our aim is to involve entire families. Participation will, however, be also possible for pairs consisting of just one parent with a mental health disorder and one child aged 6–18. For children aged under 18, parental consent is required for their participation in the study. Participants will receive a timeline regarding the survey measures and delivery of the ChildTalks+ intervention. They will receive reminders of upcoming meetings.

Families will pay nothing for their participation in the project and receive no financial reward. Trained therapists will be financially rewarded for their work with families: the remuneration will cover a total of 10 h of work with each family. This includes direct work with the family using the ChildTalks+ methodology and administration of questionnaires (handing them out, providing instructions for completion, collection of completed questionnaires, and their delivery to coordinators of the implementation team).

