### Sample size and power calculation

Power analysis was computed based on the Model Protocol by Reedtz et al [28] We hypothesized that the within-subject change of the outcome between T0 and T1 should differ by about 2.5 between the intervention and the control group, with a pooled SD of the scores app. 4.90. For the power analysis, a simple two-tailed paired t-test with significance level of 5% was used to get a power of 0.8 with an estimated sample size of 33 pairs. Trained therapists will offer participation to 80–88 families, thus allowing for some attrition. A total of 66 families will be assigned to the intervention (*N* = 33) or control (*N* = 33) group.

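### The power calculation and the mixed model make no allowance for therapist; if therapists treat several intervention families and results differ between them, standard errors are too small and 80% power is not reached

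*Protocol article*

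**What the plan says.** Under Statistical methods, the change from T0 to T1 is compared between groups with a "linear mixed-effects model with two nested random effects, where the paired families will be first level no. 1 and the family" is the second level. The same model is then used for T0 to T2 and T0 to T3, with Holm's adjustment. The model is also to be adjusted for factors thought to influence the outcome, none of which is named.

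Under Sample size and power calculation, the change "should differ by about 2.5 between the intervention and the control group", "with a pooled SD of the scores app. 4.90", and "a simple two-tailed paired t-test with significance level of 5% was used to get a power of 0.8", giving "an estimated sample size of 33 pairs".

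On delivery, the section on the ChildTalks+ intervention has one trained therapist conduct the sessions with a family. Procedure pays therapists per family: "the remuneration will cover a total of 10 h of work with each family". Study settings has new therapists trained in each of three recruitment waves. The Control group section delays the intervention until after T3. Allocation into groups matches on the number of risk factors and does not mention the therapist.

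**The concern.** Two intervention families in different matched pairs can share a therapist. If some therapists obtain better results than others, the changes in those two families are correlated. The pair effect does not absorb this, because the families belong to different pairs. The family effect does not absorb it either, because it is specific to one family. Control families receive no sessions before T3, so this delivery effect falls on one arm and does not cancel in the comparison.

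Two things are at stake. A test that ignores the component can reject too often, and a test that includes it has less power than stated. Because one model serves all three time points, the understatement would enter every test, and Holm's method does not repair p-values that are individually too small. The article also hopes that positive results will support wider use of the programme, by other professionals, so variation between therapists belongs in the reported uncertainty.

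**Working it through.** **Inputs from the article.** Difference in change 2.5; SD 4.90, read as the SD of the within-pair difference because that reading reproduces the printed number; two-sided 5% paired t-test; target power 0.80; 33 pairs.

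**Inputs assumed.** The number of intervention families per therapist, m (1 to 6), and the therapist ICC (0.05 and 0.10), meaning the share of variance in an intervention family's change that is due to the therapist. The article gives neither. Each arm is assumed to contribute half of the variance of the pair difference.

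**Step 1: reproduce the plan.** The normal approximation is ((1.96 + 0.84) × 4.90 / 2.5)² = 30.2, so 31 pairs. The exact calculation uses the noncentral t with n − 1 degrees of freedom and noncentrality (2.5 / 4.90) × √n. It gives power 0.798 at 32 pairs and 0.811 at 33. The printed 33 is therefore reproduced, as the smallest number that reaches 0.80 when pairs are independent.

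**Step 2: variance with therapist clustering in one arm.** Clustering multiplies the intervention arm's half of the variance by 1 + (m − 1) × ICC and leaves the control half unchanged. The variance of the mean pair difference is therefore multiplied by

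DE = ½ × [1 + (m − 1) × ICC] + ½ = 1 + (m − 1) × ICC / 2.

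**Step 3: consequences.** Power is recomputed with SD 4.90 × √DE. The correct interval is wider by the factor √DE. The type I error of a test that ignores the therapist is the two-sided tail of t with 32 degrees of freedom beyond 2.037 / √DE. Example for m = 4, ICC 0.10: DE = 1 + 3 × 0.10 / 2 = 1.15; √1.15 = 1.072; 2.037 / 1.072 = 1.90, a two-sided tail of 6.7%.

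| m | ICC | DE | Interval width factor | Power at 33 pairs | Pairs for 0.80 | Type I error if ignored |
|---|---|---|---|---|---|---|
| 1 | any | 1.000 | 1.000 | 0.811 | 33 | 5.0% |
| 2 | 0.05 | 1.025 | 1.012 | 0.802 | 33 | 5.3% |
| 3 | 0.05 | 1.050 | 1.025 | 0.792 | 34 | 5.5% |
| 3 | 0.10 | 1.100 | 1.049 | 0.773 | 36 | 6.1% |
| 4 | 0.05 | 1.075 | 1.037 | 0.783 | 35 | 5.8% |
| 4 | 0.10 | 1.150 | 1.072 | 0.755 | 37 | 6.7% |
| 6 | 0.05 | 1.125 | 1.061 | 0.764 | 36 | 6.4% |
| 6 | 0.10 | 1.250 | 1.118 | 0.720 | 40 | 7.8% |

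These power figures do not include the further loss of degrees of freedom that comes with few therapists.

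**The case against.** A reader might infer that the intervals are too narrow as a matter of fact. The article does not show that. It gives no number of therapists, no caseload and no ICC. Payment per family allows several families per therapist but does not establish it, and with one intervention family each there is no such effect. The conclusion must stay conditional.

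Several further points narrow the likely size:

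- New therapists join in each of three waves. If the plural means at least two per wave and all of them treat intervention families, the average is at most 33 / 6 = 5.5. Larger average caseloads look unlikely, although uneven caseloads are possible.
- Intervention integrity describes a manual, a two-day training led by the programme's authors, supervision and session checklists. These may keep the ICC low; they do not show that it is zero.
- The therapist criterion "ability to adapt the content and language of sessions to the type of parent’s disorder and the age group" might be taken as evidence of variation between therapists. It is not: that adaptation follows the family's characteristics.
- Therapists recruit the families and administer the questionnaires, so effects common to both arms would partly cancel. Only variation in delivery is counted above. It would be too harsh to treat the whole pair difference as clustered, which at m = 6 and ICC 0.10 gives DE 1.50 and power 0.641, because control families receive no sessions.
- The type I error figures describe a null in which therapists differ but their average effect is zero.

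The unnamed adjustment factors could include the therapist, and covariate lists are commonly left to an analysis plan. That does not settle the matter, because the article positively fixes the random effects at two levels and sizes the trial on independent pairs.

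**Conclusion.** The point holds in conditional form. As written, neither the model nor the power calculation accounts for the therapist, who delivers the intervention in one arm only. If therapists treat more than one intervention family and outcomes vary by therapist, the standard error of the group difference is too small and 80% power is missed.

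The size depends on two quantities that the article does not give. With up to three families per therapist and an ICC up to 0.05, the loss is under 2 points of power and at most one further pair would be needed. It becomes material at about four families per therapist with ICC 0.10, a loss of 0.811 − 0.755, or about 5.6 points. With six families and ICC 0.10 the loss is about 9 points. The design has almost no margin to absorb this, since 32 independent pairs already fall just below 0.80. The article does not support a claim that the trial is seriously underpowered or that its test is certainly anti-conservative.

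**What to change.** **Statistical methods.** Add a therapist random effect for families receiving ChildTalks+ (partially nested, crossed with pair), acting on the change from baseline, and use Satterthwaite or Kenward-Roger degrees of freedom. If the variance is not estimable, report a therapist-clustered analysis with a small-sample correction as a sensitivity check.

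**Sample size and power calculation.** State that 80% power assumes no clustering by therapist. Give the expected number of therapists and of families per therapist, and the power at that caseload over a range of ICCs.

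**Cost.** About one sentence in each section. The therapist should be identifiable from the per-family payment and the session logbooks. The price is slightly wider intervals, a slightly lower stated power, and an imprecise variance component if therapists are few. The change discloses any loss of power; it does not recover it.

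### The 80% power is computed for one T0–T1 test at an unadjusted 5%, but that test is Holm-adjusted with at least two others, which leaves about 66–76% on the plan's own inputs

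*Protocol article*

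**What the plan says.** Under Sample size and power calculation, the assumed difference in change from T0 to T1 "should differ by about 2.5 between the intervention and the control group", "with a pooled SD of the scores app. 4.90". The calculation uses one two-tailed paired t-test at 5% "to get a power of 0.8 with an estimated sample size of 33 pairs". The result is 66 families in two groups of 33. The scale that carries the 2.5 and the 4.90 is not named.

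Under Statistical methods, the T0–T1 hypothesis is tested with a linear mixed-effects model adjusted for covariates. The T0–T2 and T0–T3 hypotheses are assessed in the same way, and P-values "will be adjusted for multiple comparisons using the Holm’s method". The section does not say which tests form the Holm family. It neither exempts T0–T1 from the adjustment nor places it first.

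Under Measures, seven instruments are listed without ranking: KIDSCREEN-27, the Parent–Child Communication Scale, PSOC, PEDS, ChEDE-Q, SDQ and YMHL. Two of these have separate parent and child reports. Nothing in the article's text names a primary outcome.

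**The concern.** The test that was powered is not the test that will be run. The sample size gives T0–T1 the whole 5%, while the testing rule makes it share that 5% with at least T0–T2 and T0–T3. A real effect of the assumed size would then be missed at T1 in roughly a quarter to a third of such trials, not the one in five that the article states.

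A second question follows from the unnamed outcome. If the Holm family spans several instruments, power at T1 falls further. If the family is only the three time points within each outcome, nothing holds the error rate at 5% across instruments. The article does not say which applies.

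**Working it through.** **Inputs from the article.** Difference 2.5; SD 4.90; 33 pairs; two-sided 5%; target power 0.8 (Sample size and power calculation). Three time contrasts and Holm (Statistical methods). Seven instruments (Measures).

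**Assumptions.** The 4.90 is taken as the SD of the within-pair difference in change, because that use reproduces 33 pairs. Correlations between tests are not given, so a range is shown.

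**Step 1: the plan's own figure.** For a paired t-test, the noncentrality is (difference/SD) × √n with n − 1 degrees of freedom. Here 2.5/4.90 = 0.510, and 0.510 × √33 = 2.93 with 32 degrees of freedom. The two-sided 5% critical value is 2.037.

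| Pairs | Power at 5% |
|---|---|
| 32 | 0.798 |
| 33 | 0.811 |

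So 33 is the smallest number that reaches 0.8 at an unadjusted 5%. The figure is right for that test and contains no allowance for multiplicity.

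**Step 2: Holm over the three time points of one outcome.** Holm compares the smallest P-value with 0.05/3 = 0.0167, the next with 0.05/2 and the largest with 0.05. At 0.0167 the critical value rises to 2.526 and power with 33 pairs is 0.657. Reaching 0.8 at that level takes 44 pairs (88 families).

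The later steps are more lenient, so the full Holm procedure was simulated with three paired t-tests, n = 33:

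| Assumed correlation | T1 power, effect at T1 only | T1 power, equal effects at all three times |
|---|---|---|
| 0 | 0.66 | 0.76 |
| 0.5 | 0.66 | 0.74 |
| 0.8 | 0.66 | 0.73 |

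Every cell is below 0.80.

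**Step 3: if the family also spans instruments.** Assuming one score per instrument and 33 pairs for each, there are 7 × 3 = 21 tests. The first step is 0.05/21 = 0.0024, where power is 0.376; simulated Holm power at T1 is 0.37–0.49. This shows the direction only, because several instruments will not have 33 pairs.

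**Step 4: if Holm is applied separately within each outcome.** Each outcome then carries its own 5%. With seven independent outcomes and no true effects, the chance of at least one false claim is 1 − 0.95⁷ = 0.30. At correlations of 0.3, 0.5 and 0.8 between outcomes it is 0.27, 0.23 and 0.15.

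**Step 5: how much covariates would have to contribute.** Suppose the covariates remove a fraction r of the variance, so that the SD becomes 4.90 × √(1 − r). With equal effects and correlation 0.5, simulated T1 power under Holm is 0.79 at r = 10% and 0.82 at r = 15%. With an effect at T1 only, r must be about 25% (power 0.80). The article gives no value for r.

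**The case against.** The strongest reply is that the Holm family is detail that an article may leave to an analysis plan. Both sections speak of one outcome in the singular, and the sample size covers T0–T1 only, so the plan may intend T0–T1 of a single outcome as the lead test at a full 5%. The text does not exclude this, and it would restore the 80%. It does not state it either: the adjustment follows directly on the three hypotheses and exempts none. Any Holm family that contains the three time points breaks the stated power. The conflict is therefore between two things the article does state, and not a matter of missing detail.

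A second reply is that the mixed model is adjusted for covariates while the power calculation rests on a simple t-test. This stands in part. A variance reduction of 10–15% would roughly close the gap if effects are equal at all three times, but about 25% is needed if the effect is at T1 only. The shortfall is thus conditional, and the article claims no such gain.

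A third reply is that a primary outcome may be named in the study design figure, the registry record or the model protocol on which the power analysis draws, none of which is available here. This also stands. What can be said is that the article's text names none. A reader might infer that any of the seven instruments could be put forward afterwards as the outcome; that cannot be confirmed from this document.

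**Conclusion.** The point holds in a limited form. The stated 0.8 belongs to a test that the stated rule does not run. With 2.5, 4.90 and 33 pairs, T1 power is about 0.66 (effect at T1 only) to 0.73–0.76 (equal effects, correlations 0–0.8), before any covariate gain. It is lower if the family crosses instruments. If Holm stays within each outcome, error over seven outcomes is roughly 15–30%, depending on the assumed correlation.

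Three stronger readings are not supported:

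- A reader might infer that power collapses to about a third, for example 0.34 at the first step over nine reports × three times = 27 tests. That figure is a first step and not Holm power. It also counts PEDS, which yields risk groups and covers ages up to 8, and gives a full 33 pairs to child reports limited to those over 15.
- A reader might quote 30%, or 37% over nine reports, as the error rate. Both assume independent outcomes, which is implausible for questionnaires from the same families.
- A reader might object that 2.5 and 4.90 cannot fit scales as different as T-values and risk categories. The article applies them to one outcome and never to all seven. The fair complaint is only that the scale is unnamed.

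This should be fixed, but it does not invalidate the trial.

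**What to change.** Name the one outcome to which the 2.5 and 4.90 apply, and do so before outcome data are examined. Because registration was retrospective, the date of that decision should be recorded. Make its T0–T1 difference in change the primary test at two-sided 5%, outside the Holm family. Apply Holm to T0–T2, T0–T3 and the other outcomes as secondary, and list the tests in that family. The choice of scale is the sponsor's; one that every family provides is preferable, so that all 33 pairs contribute.

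If no primary outcome is named, restate the power at the Holm-adjusted level: about 0.66–0.76 for three time points, with the assumed pattern of effects and correlation. Any credit for covariates should come with a stated variance reduction.

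The first option changes wording in the protocol, the analysis plan and, where needed, the registry entry, and needs no more families. Its cost is that the other instruments become secondary. The second option costs a less favourable power statement.

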### Assessments

The data will be collected using a variety of questionnaires (described under measures). The questionnaires are completed by parents of children aged 6–18 and children aged 12 and older. Two questionnaires on the list, namely *The Strengths and Difficulties Questionnaire (SDQ)* and *The Youth Mental Health Literacy Scale (YMHL)*, will be completed by children over the age of 15. For children under 12 years of age, the Ethics Committee of the General University Hospital (Prague, Czech Republic) allowed qualitative data to be collected through interviews with the therapist. Participating parents and children will explore areas which are being assessed at the baseline, post-test (T1), and at the follow-ups (T2, T3). All assessments will be conducted using appropriate scales individually with each subject.

#### The intervention group (*N* = 33)

After the baseline assessment (T0), recruited families should receive the ChildTalks+ intervention. Two months after T0, assessment will be repeated in a post-test (T1). Parents and children should also receive a follow-up assessment 6 months from T1 (at T2) and 12 months from T1 (at T3).

#### Control group (*N* = 33)

Two months after the baseline assessment (T0), post-test assessment (T1) should be performed at the same time as the T1 assessment of the intervention group. Parents and children have a follow-up assessment 6 months from T1 (T2) and 12 months from T1 (T3). After the T3 follow-up assessment, families will receive the ChildTalks+ intervention.

In the qualitative part of the research, we also explore the use of the ChildTalks+ intervention by professionals who treat patients diagnosed with eating disorders. We will gather these qualitative data using semi-structured interviews to explore the feasibility of ChildTalks+ intervention for patients with eating disorders and their offspring, and to describe the therapists’ experiences during the collaboration, including perceived obstacles and positives. The results should also inform us about what parents and children found helpful about the ChildTalks+ intervention. The qualitative data will be assessed by a thematic analysis [65].

### Measures

*Health-Related Quality of Life (KIDSCREEN-27)* [66, 67] is a measure used to assess children’s health-related quality of life, a factor that is receiving ever more attention and is considered an important indicator of health status in both pediatric and epidemiological research. The scale is designed for children aged 8–18. It contains 27 questions divided into five subscales on how well the child feels physically and mentally, on perceived autonomy and relationships with parents, social support and relationships with peers, and the school environment. All items use the same five-point Likert scale. Scores are reported as t-values, with higher scores reflecting a higher health-related quality of life. The scale takes 10–15 minutes to complete [28].

*Parent–Child Communication Scale* [68] consists of two scales: the child report and the parent report. The Parent–Child Communication Scale assesses how children and their primary caregivers perceive each other’s openness to communication and their communication skills. The child report consists of 10 items, the parent report of 20 items. Responses are coded on a five-point Likert scale ranging from 1 (“almost never”) to 5 (“almost always”) [28].

*Parenting Sense of Competence (PSOC)* [69, 70] is a scale containing 17 questions for parents who have a child or children aged 6–18. There is a version of the questionnaire adapted for mothers and for fathers. The aim of the scale is to assess how accurately parents perceive their ability to do the job of parenting their children. The scale contains factors that reflect satisfaction and efficiency, where satisfaction reflects parents’ motivation, anxiety, and frustration, while effectiveness reflects parenting competence, including problem-solving skills. Subscales are rated on a 6-point scale from 1 (“strongly agree”) to 6 (“strongly disagree”). This measure does not differentiate based on the children’s age or gender. It has been demonstrated that this scale has an adequate reliability for use with parents [28].

*Parental Evaluation of Developmental Status (PEDS)* [71, 72] is a scale designed for parents of children aged from 21 months to 8 years. It consists of 10 questions. In answering them, parents describe their concerns regarding significant emotional or behavioral problems related to their children’s development. If parents’ concerns are carefully identified, they can help detect mental health difficulties in the child’s development. This scale enables a categorizarion of children into risk groups for developmental disorders based on different types of parental concerns. In other words, the measure helps determine whether children are at a high, medium, limited, or no risk of developmental problems. Previous studies have established that the measure’s reliability scores are adequate [28].

*Eating Questionnaire – Youth version (ChEDE-Q)* [73, 74] contains 39 questions validated for children aged 6–18. The questions focus on the child’s eating habits, relationship with own body, and physical activity. Children answer them according to the reality of the past 28 days. By analysing the answers, one can obtain information about the child’s risk of developing eating disorders.

*The Strengths and Difficulties Questionnaire (SDQ)* [75, 76] is a scale used to assess the strenghts and weaknesses of children aged 6–18. The Ethics Committee of the General University Hospital in Prague had decided that it can only be administered to children over 15 years of age. This screening questionnaire consists of 25 questions divided in five areas: emotional symptoms, conduct problems, hyperactivity and inattention, interpersonal problems, and prosocial behavior. This questionnaire is completed separately by parents and children. Responses to the statements are rated on a three-point Likert scale (“not true,” “somewhat true,” “certainly true”). According to the prevalence of clinical disorders, children with higher total difficulty scores show greater psychopathology. Previous studies have shown that this scale’s reliability scores are adequate, and the measure is considered a dimensional tool for assessing children’s mental health [28].

*Youth Mental Health Literacy Scale (YMHL)* [33] scale examines children’s awareness of mental health (common mental illnesses/holistic recovery), mental illness stigma, coping and help-seeking for self or other people who may be experiencing what could be mental health symptoms. Children’s knowledge of mental health and recovery measures can be used for the general population and/or the COPMI [33]. The scale was originally developed for children aged 11–16. For the purpose of the pilot study in the Czech Republic, the measure’s authors agreed that it could be administered to children aged 11–18 who would be divided in two groups (11–14 years and 15–18 years). But the Ethics Committee of the General University Hospital in Prague had decided that it can only be administered to children over 15 years of age.

